#### CVD mortality

This is defined as any documented death caused by CVD during the study period.

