#### Secondary outcomes

Secondary outcomes of the trial are:

1. Smoking cessation rate at the 6-month follow-up, proven by measurement of (ppmCO).

2. CVD risk measured by the Framingham general cardiovascular risk score at the 12-month follow-up.

3. Blood pressure and heart rate measured at the 6- and 12-month follow-up.

4. Number of CVD events and deaths at the 12-month follow-up.

5. Cost-effectiveness of the health service packages at the 12-month follow-up.

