#### CVD events and death

Participants will be followed up by nurse-administered, structured questionnaires at the 6- and 12-month visits, ascertaining medical history, lifestyle and health-related behaviors. During each questionnaire, participants will be asked whether they have had a CVD event referred to the community hospital; any reported CVD event will be confirmed by reviewing the NCD network medical records [25].

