### Sample size

A total of 328 participants will be randomized to have 164 in the new service arm and 164 in the routine service arm. The sample size for the randomized controlled trial was calculated to have a power of 80% and 95% confidence interval so as to show the difference in primary and secondary outcomes, and the CVD incidence between the new package arm and the routine service arm. It was calculated using the power sample size calculation of Stata version 11, based on the previous year’s smoking cessation rate at the MH (9%), and the estimated cessation rate of the evidence-based package (24%). Additionally, the calculated sample size was increased by 20% to compensate for loss to follow-up.

The sample size for the additional non-randomized arm was calculated at a ratio of 1:3 compared to the total size of the two intervention arms. The power of 90% and 95 percent confidence interval will suffice to see the difference in CVD events between ex-smokers and continuous smokers, assumed as 0.1 and 0.25. Totally the sample size is 440 participants.

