	**Follow-up**												
Visit number	1	2	3	4	5	6	7	8	9	10	11	12	13
Month	0	1	2	3	4	5	6	7	8	9	10	11	12
Inclusion and exclusion criteria	x												
Framingham scoring	x						x						x
Self-reported smoking cessation	x			x			x						x
Smokerlyzer	x						x						x
Fagerstrom Test	x						x						x
Blood pressure	x	x	x	x			x			x			x
BMI	x			x			x						x
Blood glucose	x						x						x
Waist circumference	x						x						x
Hip circumference	x						x						x
HbA1C	x												
Lipid profile	x												
CVD event	x						x						x
CVD death	x						x						x
Questionnaires													
Demography	x												
Questionnaire assessing motivation to stop smoking (MTSS)	x						x						x
Questionnaire assessing cost effectiveness	x						x						x
Questionnaire assessing family support on smoking cessation	x						x						x
Questionnaire assessing health literacy	x						x						x

Moreover, the intervention design is an add-on design in which additional evidence-based components are added to the existing routine service [30]. Regarding the outcome measurement, most of the secondary outcomes are feasible to measure via the routine data collection of the study site hospital network. Furthermore, the sample size has been increased by 20% to compensate for dropouts.

The study is carefully designed randomized controlled trial, evaluating two approaches of active intervention and comparing the rate of behavior change. However, the CVD outcome event rate of the active intervention arms will also be analyzed and compared with that of the non-randomized arm made up of smokers refusing to try to give up smoking. It will require the adjustment of minimal residual confounders. Moreover, there will be different models of covariates used to analyze different outcomes. For instance, adjustments in the comparison of CVD events and deaths between the intervention and control arms may include family history, lifestyle, physical activity, alcohol consumption, dietary habits, current medications and socioeconomic status [25]. To assess physical activity as a covariate, a rapid physical activity assessment scale will be applied [31]. Therefore, possible confounders are collected and will be adjusted appropriately in later analysis [32] (Table 3).

**Table 3 T3:** Confounder measurements

**Confounder**	**Variables**	**How to measure**
Demographic characteristics	Age, sex, social status, family size, educational attainment, occupational history, income	Questionnaire

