#### CVD risk, CVD events and CVD death

CVD risk via FMH scores, blood pressure, heart rate and BMI will be compared between those successfully giving up smoking and continuous smokers by adjusting covariates. Moreover, the time event analysis approach will be applied to compare the CVD events and CVD deaths between the two intervention arms. Those outcomes will then be analyzed among the three arms of the study by applying the Cox regression model.

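### CVD events can be missed because records are reviewed only to confirm what a participant reports at the 6- or 12-month visit

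*Protocol article*

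**What the plan says.** Under Outcome measurements, the section on CVD events and death sets the procedure. "Participants will be followed up by nurse-administered, structured questionnaires at the 6- and 12-month visits", and at each interview "participants will be asked whether they have had a CVD event referred to the community hospital; any reported CVD event will be confirmed". That check is made against the network's records. The question covers only events referred to the community hospital. Table 2 ticks CVD event and CVD death at months 0, 6 and 12 and at no other visit.

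Two other places bear on how events are found. The definition of CVD mortality reads: "This is defined as any documented death caused by CVD during the study period". The Follow-up section remarks that "most of the secondary outcomes are feasible to measure via the routine data collection of the study site hospital network".

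The outcome at issue is the fourth secondary outcome: "Number of CVD events and deaths at the 12-month follow-up". The Analyses plan states that "the time event analysis approach will be applied to compare the CVD events and CVD deaths between the two intervention arms", followed by Cox regression across all three arms. On attrition, the Sample size section says that "the calculated sample size was increased by 20% to compensate for loss to follow-up", while the Follow-up section expects little dropout.

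**The concern.** A record review that starts from a self-report can remove false reports but cannot recover unreported events. Someone who has had a disabling stroke, has died or has stopped attending is less able to report, and such people may well include a disproportionate share of those with events. The plan names no proxy interview, no tracing of missed visits and no search of everyone's records.

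At stake are the count in secondary outcome 4 and the comparisons built on it: the two randomized arms, and then the three arms including those who refused to try quitting. The Analyses plan also promises intention-to-treat for all pre-specified outcomes, which is hard to honour for an outcome that is observed only in people who attend. Under-counting costs events and power in every case. Whether it also distorts the comparison between arms depends on conditions worked through below.

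**Working it through.** The protocol gives no figure for completeness of event capture, so there is none to reproduce. The check has two parts.

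**Reading the sections together**

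- The section on CVD events and death is the only one that describes how events are found. Its trigger is a report by the participant: "any reported CVD event will be confirmed by reviewing the NCD network medical records".
- The CVD mortality definition implies a documentary source for deaths but names no source and no search.
- The Follow-up remark on routine hospital data speaks of feasibility. It neither commits the trial to an event search nor rules one out.
- No section describes a route to an event in a person who is not interviewed.

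**Illustration of size**

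Input from the protocol: 164 per randomized arm. Assumptions, because the documents do not give them: true 12-month risk r = 10% in both arms; a proportion *a* attends; non-attenders have *k* times the risk of attenders, with *k* the same in both arms; every event in an attender is reported.

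- Risk in attenders: p = r / (a + (1 − a)k)
- Observed risk with all randomized in the denominator: a × p
- Observed risk with attenders only in the denominator, a rough stand-in for censoring non-attenders: p

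With full capture, 164 × 0.10 = 16.4 events are expected per arm. At 80% attendance in both arms:

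- k = 1: 164 × 0.080 = 13.1 found
- k = 2: 0.80 × 0.10/1.2 = 0.0667, so 10.9 found
- k = 3: 0.80 × 0.10/1.4 = 0.0571, so 9.4 found

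The risk ratio is 1.00 in all three cases.

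With unequal attendance (new arm vs routine arm):

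| Attendance | k | Observed risk, all randomized | Ratio, all randomized | Ratio, attenders only |
|---|---|---|---|---|
| 85% vs 75% | 1 | 8.5% vs 7.5% | 1.13 | 1.00 |
| 85% vs 75% | 2 | 7.4% vs 6.0% | 1.23 | 1.09 |
| 85% vs 75% | 3 | 6.5% vs 5.0% | 1.31 | 1.15 |
| 90% vs 70% | 1 | 9.0% vs 7.0% | 1.29 | 1.00 |
| 90% vs 70% | 2 | 8.2% vs 5.4% | 1.52 | 1.18 |
| 90% vs 70% | 3 | 7.5% vs 4.4% | 1.71 | 1.33 |

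Worked line for 90% vs 70%, k = 2: 0.90 × 0.10/1.1 = 0.0818 and 0.70 × 0.10/1.3 = 0.0538, ratio 1.52; attenders only, 0.0909/0.0769 = 1.18. The ratios do not depend on r, because r cancels. The arm that attends better looks worse.

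**Effect on power**

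The Sample size section assumes CVD event proportions of 0.10 and 0.25 for ex-smokers and continuing smokers. For illustration only, put these in two groups of 164, with a two-sided 5% level and the usual normal approximation: z = (difference − 1.96 × pooled SE) / unpooled SE.

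- Full capture: (0.15 − 1.96 × 0.0420)/0.0411 = 1.65, power 95.0%.
- 80% capture in both groups, so 0.08 vs 0.20: (0.12 − 1.96 × 0.0383)/0.0377 = 1.19, power 88.3%.

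**The case against.** The strongest reply is that the plan leaves room for better capture than the interview alone. A death cannot be self-reported. It has its own row in Table 2 and its own definition resting on documentation, so the interview trigger need not govern deaths. A full protocol may describe the tracing that a condensed article omits. Participants are long-term clients of the clinics, and dropout is expected to be limited. This stands to the extent that one can say only that events can be missed. A reader might infer that all events in those who die or are disabled are lost; the text does not support that. The reply does not remove the point, because the procedure the article does state runs from report to record.

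A reader might also infer that the comparison of arms is biased. The documents do not show it.

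- **Contact.** The routine arm is not seen only at months 0, 6 and 12; those are its advice visits in Table 1. Table 2, which covers all three arms, schedules blood pressure at months 0, 1, 2, 3, 6, 9 and 12, and routine-arm patients are reminded at successive visits for a year. The monthly nurse contact in the new arm is set for 3 months. The arms do differ in intensity and family support, and the refusers get no cessation service, so differential attendance is possible, but no figure supports it.
- **Ratios.** The values 1.13 and 1.29 treat every unobserved participant as event-free and so fit only raw counts over all randomized. A time-to-event analysis would ordinarily censor these people; with equal risk in attenders and non-attenders the ratio is then 1.00.
- **Blinding.** The Blinding section says the primary care unit nurse knows the arm, but the outcome interview is described only as nurse-administered. Since reports are confirmed in records, knowledge of the arm could affect how fully events are elicited but could hardly create false ones.

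**Conclusion.** The point holds as a weakness in how events are found. As written, the procedure can miss CVD events in people who do not attend or do not report, and it names no way of finding deaths. The certain consequence of any missed events is an under-count of secondary outcome 4 and less information for its time-to-event and Cox comparisons. If 20% of each arm went unobserved at equal risk, about 3.3 of 16.4 events per arm would be missed (16.4 − 13.1) at an assumed 10% risk. That 20% borrows the sample-size allowance; it is not a forecast.

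Bias between arms is conditional. It requires attendance or reporting to differ by arm and, when non-attenders are censored, a different event risk in them too. If the new arm attended better and non-attenders were at higher risk, the distortion would run against the new package. CO-verified cessation, the primary outcome, is not affected. This is a worthwhile, inexpensive improvement to a secondary outcome and does not threaten the main conclusion.

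**What to change.** Add to the section on CVD events and death that, at month 12, the NCD network and hospital records of every participant in all three arms (about 440) will be searched for CVD events and deaths, regardless of self-report or attendance. Use the recorded date as the event time in the time-to-event and Cox analyses. Keep the 6- and 12-month questionnaire as a supplementary source, mainly for events treated outside the network. If the full protocol already provides such a search, say so in this section.

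The cost is modest clerical time in a network already used to confirm reports, with no new visit or procedure. Out-of-network events may still be missed.

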#### Waist and hip circumference measurement

Waist and hip circumference will be measured at the baseline, 6- and 12-month visits. Stretch-resistant, standard measuring tapes will be provided to nurses to perform the waist circumference and hip circumference measurement. Waist circumference measurement will be made at the approximate midpoint between the lower margin of the last palpable rib and the top of the iliac crest, at the end of normal expiration, according to the WHO protocol [26]. The hip circumference will be measured around the widest portion of the buttocks [26].

### Sample size

A total of 328 participants will be randomized to have 164 in the new service arm and 164 in the routine service arm. The sample size for the randomized controlled trial was calculated to have a power of 80% and 95% confidence interval so as to show the difference in primary and secondary outcomes, and the CVD incidence between the new package arm and the routine service arm. It was calculated using the power sample size calculation of Stata version 11, based on the previous year’s smoking cessation rate at the MH (9%), and the estimated cessation rate of the evidence-based package (24%). Additionally, the calculated sample size was increased by 20% to compensate for loss to follow-up.

The sample size for the additional non-randomized arm was calculated at a ratio of 1:3 compared to the total size of the two intervention arms. The power of 90% and 95 percent confidence interval will suffice to see the difference in CVD events between ex-smokers and continuous smokers, assumed as 0.1 and 0.25. Totally the sample size is 440 participants.

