### Analyses plan

All analyses for pre-specified outcomes in the trial protocol will strictly follow the intention-to-treat principle [33]. Statistical significance in all statistical analysis will be taken as a *P* value less than 0.05 with a 95% confidence interval. Relative risk (RR) for achieving primary outcome, smokerlyzer-confirmed smoking cessation, will be reported with the 95% confidence interval. Moreover, the number needed to treat (NNT) for achieving smokerlyzer-confirmed smoking cessation by the two intervention arms will be reported [34]. To overcome the contamination of the intervention, complier average causal effect (CACE) analysis will necessarily be applied.

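### The stated inputs (9% vs 24%, 80% power, 20% allowance) give 114 to 135 per arm, not 164; the trial is not underpowered, but the basis for its size cannot be traced

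*Protocol article*

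**What the plan says.** The Sample size section fixes the size of the randomized part of the trial: "A total of 328 participants will be randomized to have 164 in the new service arm and 164 in the routine service arm". The number was "calculated to have a power of 80% and 95% confidence interval" with the sample-size routine of Stata 11. The planning rates are 9% cessation under routine care, taken from the hospital's previous year, and 24% under the new package. The section then adds: "Additionally, the calculated sample size was increased by 20% to compensate for loss to follow-up". The Follow-up section repeats the 20% increase and gives no other allowance.

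The Sample size section also says that the number is meant to show differences in secondary outcomes and in CVD incidence between the two arms, but gives no between-arm rates for these. A separate calculation (90% power, 0.1 vs 0.25) is given for CVD events in ex-smokers against continuous smokers, in the paragraph on the non-randomized arm. The Analyses plan sets significance at P below 0.05 and compares cessation between the arms by a chi-square test.

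**The concern.** Every quantity needed to rebuild the number is printed except the sidedness of the test and the use of a continuity correction, and both can be tried each way. A stated sample size should then be reproducible to within rounding. This one is not, and the gap is too wide to be explained by the choice of formula.

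Cessation at 1 year is the primary outcome. If the number does not follow from its inputs, a reader cannot say what difference the trial was sized to detect, or with what power. The 80% printed in the plan is not the power of the design at its own planning rates.

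**Working it through.** **Inputs.** From Sample size: p1 = 0.09, p2 = 0.24, difference d = 0.15, power 80%, equal arms, 20% increase. From Analyses plan: alpha 0.05. A two-sided test is assumed from the 95% confidence interval, because sidedness is not stated.

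**Step 1: evaluable number per arm, no continuity correction.**

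n = [1.96 × √(2 × p̄ × q̄) + 0.8416 × √(p1q1 + p2q2)]² / d², with p̄ = 0.165 and q̄ = 0.835.

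- 2 × 0.165 × 0.835 = 0.27555, square root 0.5249; × 1.96 = 1.0288
- 0.09 × 0.91 + 0.24 × 0.76 = 0.2643, square root 0.5141; × 0.8416 = 0.4327
- n = (1.4615)² / 0.0225 = 94.9, so **95**

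**Step 2: with continuity correction.**

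n' = (n/4) × [1 + √(1 + 4/(n × d))]² = (94.9/4) × [1 + √(1 + 4/14.24)]² = 107.9, so **108**.

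**Step 3: the 20% allowance.** The text describes an increase (× 1.2). Dividing by 0.8 is also tried.

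| Formula | Evaluable per arm | × 1.2 | / 0.8 | Shortfall against 164 |
|---|---|---|---|---|
| Uncorrected | 95 | 114 | 119 | 50 / 45 |
| Continuity-corrected | 108 | 130 | 135 | 34 / 29 |

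The plan's 164 is not reproduced. The gap is 29 to 50 per arm, or 58 to 100 over both arms.

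**Step 4: other variants at 80% power.** Unpooled-variance and arcsine formulas give 110 to 115 after the allowance. One-sided tests give 90 to 110. None exceeds 135. To go from 108 to 164 needs an increase of 164/108 − 1 = 52%, or a dropout of 1 − 108/164 = 34% if the number is divided by the retained fraction.

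**Step 5: the power the design has at 9% vs 24%.** After 20% loss, 164 × 0.8 = 131 per arm.

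Power = Φ{[d√n − 1.96√(2p̄q̄)] / √(p1q1 + p2q2)}; with continuity correction, d is replaced by d − 1/n.

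- n = 131: (0.15 × 11.446 − 1.0288)/0.5141 = 1.338, power **91.0%**; corrected, 87.9%
- n = 164: (0.15 × 12.806 − 1.0288)/0.5141 = 1.735, power **95.9%**; corrected, 94.3%

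**The case against.** The strongest reply is that 80% and 24% may both be right as minimum requirements. The section says that the number also serves secondary outcomes and CVD incidence, so something other than cessation may have driven it. This stands in part. It defeats the inference, which a reader might draw, that either the stated power or the stated effect must be wrong. Several single changes come close to 164:

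- 90% power with continuity correction: 140 × 1.2 = 168.
- Two-sided alpha of 0.025 with correction: 129/0.8 = 162.
- The 0.10 vs 0.25 calculation at 90% power, uncorrected: 133 per arm, giving 160 or 167.
- 9% vs 22% at 80% power with correction: 136 × 1.2 = 163.2, which rounds up to 164.

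The last is tempting because it lands exactly, but 22% is back-solved and appears nowhere in the article, where the only planned rate for the new package is 24%. The documents cannot select among these routes.

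The reply does not rescue the text. The section says that the number was based on 9% and 24% cessation, and it gives no between-arm CVD rates. If CVD events set the number, the stated basis is itself wrong.

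A second reply is that the error is harmless: the 80% target is exceeded, and the result will be read from the relative risk and its confidence interval. That stands as to validity, and no analysis or decision rule rests on the 80%. It does not make the printed figure correct.

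**Conclusion.** The point holds as a sample-size statement that its own inputs do not reproduce. The inputs give 114 to 135 per arm against a stated 164, so at least one input (power, effect, alpha or allowance), or the outcome on which the number is said to rest, is wrong as written. The article does not show which.

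A reader might infer that the trial is underpowered. It is not: under its own rates the power for cessation is about 88-91% with 131 evaluable per arm and 94-96% with no loss, against the stated 80%. Nor should the excess be quoted as one number, because it depends on the continuity correction and on how the 20% is applied, and the article settles only the second.

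The conclusion assumes a two-sided 5% test and 1:1 allocation. The 88-91% also assumes that a 20% loss leaves the 9% and 24% unchanged among those evaluable. A one-sided test at 80% power would widen the gap.

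**What to change.** Keep 328 randomized and change the wording of the Sample size section in one of two ways:

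1. State the outcome, rates, power, alpha, formula and allowance that produced 164, and correct whichever printed input or basis differs from them.
2. If 9% vs 24% and 20% loss stand as intended, restate the power for the primary outcome as about 88-91% with 131 evaluable per arm, saying whether the continuity correction is used.

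The first is preferable if the calculation can be recovered, because the second reports the power of the chosen number without explaining how it was chosen. Either way the cost is a few sentences. Recruitment, design and analysis are unchanged.

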### Data collection and follow-up

Since ESCAPE is a lifestyle modification trial, it requires the measuring of several outcomes and their biological and social covariates. Careful data collection and a well-designed case record form will be applied to avoid the extremes of burden on participants and insufficient data. Training, practice and revision of the case record form will precede the data collection.

#### Baseline survey

The balance between an individual’s motivation to stop smoking and his or her degree of dependence on cigarettes determines successful smoking cessation [27]. Thus, those variables will be measured at the outset of the study and at the end of the intervention. Participants will be asked to provide information about their current and past smoking status, such as the number and type of cigarettes smoked, the time they have an urge to smoke in the morning, the source of their cigarettes and details of previous attempts to give up. Breath analysis by smokerlyzer, the Fagerstrom Test for Nicotine Dependence (FTND) and the Nicodep® Test will be applied in order to assess the participant’s smoking status and nicotine dependence [20]. The smoker’s motivation will be measured by the Motivation to Stop Scale (MTSS), a single-item measure composed of key motivational constructs validated by a previous population-based study [28].

Moreover, this trial is assembled to reveal the impact of smoking cessation on the CVD risk among those most at risk. Thus, the FMH score will be measured at the outset of the study and at the end of the follow-up [23,24]. Blood pressure, heart rate, blood glucose, lipid profile, BMI, and waist and hip circumference will be measured, and these data inputs will be used to provide the FMH score [24]. The patient’s current medication for diabetes or hypertension will be recorded, as well as their food preference (salty food, fatty food) and their family history of smoking, including any known CVD events or deaths.

The new evidence-based service intervention will focus not only on the individual, but also on the social environment of the individual, such as their family support. Thus, perceived family support will be measured at the outset. Demographic and socioeconomic information of the participants will also be collected, as well as information regarding costs relating to travel, the provider, client and health service. As a covariate, individual health literacy will briefly be assessed. Measurement of this latent variable will apply communicative and critical health literacy assessment, developed and validated by Ishikawa et al. [29].

